#### Needling and injection

Under sterile conditions a skin wheal will be made using a 30-gauge needle, and 2 ml of 2% xylocaïne will be applied either behind (RCB) or below (coracoid ICB) the clavicle. A 100-mm 18-gauge echogenic needle, bevel facing up (Plexolong Nanoline; Pajunk Medizintechnik, Geisingen, Germany) will then be inserted into the skin wheal and advanced strictly in-plane with the US beam.

For RCB the needle will cross an initial blind zone measuring 3–4 cm, which corresponds to the acoustic shadow of the clavicle. For safety purposes, this length should be evaluated by checking the surface distance between the probe and initial insertion point. Once the blind zone is crossed, correct in-plane alignment should enable a precise view of the needle shaft and the tip as it advances towards the neurovascular bundle. If the initial puncture point is correct and the angle of penetration is parallel to the US probe, the shaft should point to the posterior wall of the axillary artery. Most importantly, the needle should clear the posterior wall of the clavicle and must not be angled posteriorly, to avoid any risk of pneumothorax.

For coracoid ICB, the needle will be inserted immediately under the clavicle, through the skin wheal, as established previously. The needle will be angled and advanced while aiming for the posterior wall of the axillary artery.

Hydrolocalization with 5% dextrose and neurostimulation are allowed if deemed necessary. Once the block needle tip is located adjacent to the axillary artery and posterior cord, hydrodissection using a local anaesthesia (LA) bolus will enable safe and efficient spread of LA to initially achieve the double-bubble sign [14].

Mepivacaine 1.5% (20 ml) and ropivacaine 0.5% (20 ml) will be injected in a fractionated way, while slightly adjusting the needle tip to obtain a U-shaped distribution of local anaesthetic around the axillary artery.

#### Intervention – concomitant care

Strict adherence to protocol will be mandatory to allow inclusion of patients. Thus, if any other needle or any other local anaesthetics or other volume/dose of local anaesthetics are used, the patient will be excluded from the analysis.

If the patient received more than 2 mg of midazolam (or equivalent dose of other sedative drug) during the procedure, the patient will be included only if he is still able to adequately collaborate during the evaluation of motor and sensory blockade.

This means that patients maintain adequate response to verbal commands and remain competent after the medication administration. In any circumstances, if the drugs given exceed the allowed sedation as mentioned in this protocol (fentanyl 1 μg/kg, propofol 50 μg/kg/min), the plexus block will be considered a failure.

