##### Secondary outcome measures

Imaging time: will be measured in minutes and corresponds to the time interval between contact of the US probe with the patient skin and the acquisition of a satisfactory image.Needling time: will also be measured in minutes, from the start of the skin wheal to the removal of the block needle from the tissues.Sensory loss at 10, 20 and 30 minutes: will be assessed in the territory of the radial (lateral aspect of the dorsum of the hand), median (volar aspect of the index), ulnar (volar aspect of the fifth finger), musculocutaneous (lateral aspect of the forearm), and medial cutaneous nerve of the forearm (medial aspect of the forearm) distributions using a 3-point score, where 0 = normal sensation, 1 = diminished sensation to pinpricks (hypoesthesia), and 2 = loss of sensation to pinpricks (analgesia). The sum of five scores on a maximum of 10 will be the sensory-loss final score. An independent, blinded, research assistant will complete the sensory assessment at 10, 20 and 30 minutes.Motor block at 10, 20 and 30 minutes: motor function will be tested (0 = normal strength, 1 = weakness, 2 = paralysis) for the radial (wrist extension), median (thumb-fifth finger opposition), ulnar (fifth finger abduction), and musculocutaneous (elbow flexion) nerves. The sum of the four scores on a maximum of 8 will be the motor block final score. An independent, blinded, research assistant will complete the motor assessment at 10, 20 and 30 minutes.Success of plexus block: success is a dichotomic variable answered by yes or no. Success is defined as the completion of surgery without the need for additional LA infiltration, intravenous narcotics, or general anaesthesia. However, light sedation is allowed if deemed necessary by the anaesthesiologist. Light sedation includes midazolam 1 to 4 mg intravenously, fentanyl up to 1mcg/kg. A minimum sensory score of 9/10 will be necessary to proceed to surgery without additional LA infiltration. Patients with an overall sensory score under 9/10 at 30 min will be offered general anaesthesia or supplemental blocks.Total anaesthesia time: is measured in minutes and defined as the sum of performance time and time to achieve a minimum sensory score of 9/10. It is the time for readiness for surgery.Number of block needle passes: is defined as a unit of 1, 2, 3, etc., and is the number of times the block needle will have to be realigned on the skin in order to achieve its final positioning goal under the axillary artery.Needle visualization: procedures will be videotaped and reviewed simultaneously after study completion by 2 independent anaesthesiologists skilled in US-guided regional anaesthesia using a 5-point Likert scale to rate needle visibility (1 = very poor, 2 = poor, 3 = fair, 4 = good, 5 = very good). Needle visibility will be evaluated twice. First, for RCB, assessment will be made when the needle tip is seen 1 cm after crossing the clavicle acoustic shadowing. For the coracoid ICB, the first assessment will be at a needle tip depth of 1 cm. The second needle visibility assessment will be immediately before the local anaesthetic injection, when the visibility is theoretically optimized.Needle angle: using the same videotape that we used for the evaluation of the needle visibility, we will note the angle between the needle and the upper side of the ultrasound image. It will be a continuous outcome ranging from 0 to 90 degrees.Neurostimulation use: neurostimulation is accepted if needed. However, its use other than for a safety sentinel (defined by <0.3 mA) will be recorded for subsequent analysis. It will be a dichotomous outcome.Pain during the procedure: immediately after block completion, patients will be asked to rate their discomfort associated with the procedure using a 10-cm visual analogue scale (0 = no pain, 10 = worst pain imaginable) by an independent and blinded outcome assessor.Early and late complications: the incidence of needle-induced paresthesia, vascular puncture, Horner syndrome, dyspnea, and symptoms of LA toxicity will be noted. All patients will be contacted 48 hours after surgery to ask for any delayed complications, such as dyspnea, paresthesia, weaknesses, pain at the puncture site or haematoma. Patients with complications will be followed up by our research group and a consultation in neurology may be sought.

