#### Allocation concealment mechanism

Sequentially numbered, opaque, sealed envelopes will be used to ensure concealment until enrolment is confirmed. These envelopes will be kept in the locked research assistant office and the recruiting members will have to contact this research assistant to randomize the patient. When the numbered envelope is opened, the patient is automatically included in the analysis and the numbers on each envelope ensure that all patients are enrolled after being randomized. A recruitment log will be created and exclusion will be justified for each patient excluded.

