#### Statistical methods

Analysis of the primary outcome: performance time will be analyzed with a non-inferiority test of the averages, with the objective of finding that the experimental RCB approach takes no longer to perform than the coracoid ICB approach.

The secondary outcomes will all be analyzed using superiority analysis. For continuous data or ordinal data with >8 categories, data will be compiled as average and standard deviation. If data are parametric, Student’s *t* test will be used and if not, the Mann-Whitney test will be used. For dichotomous data (block success, use of neurostimulation), the chi square or Fisher exact test will be used if n >5 or is not >5, respectively. Finally, for ordinal data the chi square test will be used if data are parametric, otherwise the Mann-Whitney test will be used.

Subgroup analysis will be conducted to evaluate if higher BMI influences the outcomes of performance time, needle visibility, number of needle passes and needle angle. Patients will be divided in two groups (of those with higher and those with lower BMI than the average BMI of all recruited patients) and analyzed according to their subgroup. If data are missing or if any patients drop out of the study, data will be analyzed using the intention-to-treat principle.

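### The protocol gives two incompatible rules on whether randomized patients with departures from the block protocol are analysed, and does not say which governs the primary non-inferiority test

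*Protocol article*

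**What the plan says.** The section Intervention – concomitant care sets two conditions that can remove a patient after allocation.

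- Departure from the study block. The section opens with "Strict adherence to protocol will be mandatory to allow inclusion of patients" and continues that if "any other needle or any other local anaesthetics or other volume/dose of local anaesthetics are used, the patient will be excluded from the analysis". The reference regimen is in Needling and injection: one specified 100-mm needle, and "Mepivacaine 1.5% (20 ml) and ropivacaine 0.5% (20 ml) will be injected in a fractionated way".
- Sedation. After more than 2 mg midazolam or equivalent, "the patient will be included only if he is still able to adequately collaborate during the evaluation of motor and sensory blockade".

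Allocation concealment mechanism states a different rule: "When the numbered envelope is opened, the patient is automatically included in the analysis". It adds: "A recruitment log will be created and exclusion will be justified for each patient excluded".

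Statistical methods has one sentence on the population: "If data are missing or if any patients drop out of the study, data will be analyzed using the intention-to-treat principle".

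Sample size enlarges the target from 49 to 55 per group to allow for dropouts and inadequate procedures. Blinding (masking) says that the operator cannot be blinded and that blinding the statistician was not thought necessary.

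**The concern.** For a randomized patient who receives another needle, drug or dose, the two rules give opposite answers. The primary analysis population is therefore fixed twice, incompatibly. With an unblinded statistician, the choice between the two could be made after the results are known.

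The direction of any bias matters because the trial seeks to show that RCB is not slower. Whether a patient departs from the regimen is settled during or after the block. If departures are commoner in long, difficult blocks, and commoner in one arm, dropping them shortens that arm's mean performance time.

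The sedation rule has a further fault. Performance time is imaging time plus needling time and ends when the needle is removed. Cooperation matters for the tests at 10, 20 and 30 minutes. A patient too sedated for those tests already has a complete primary outcome, which the rule would discard.

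**Working it through.** **1. The rules side by side**

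| Randomized patient | Concomitant care | Allocation concealment | Statistical methods |
|---|---|---|---|
| Other needle, drug or dose; data complete | Out | In | Silent: neither missing data nor dropout |
| Over 2 mg midazolam, cannot cooperate; performance time recorded | Out | In | Silent on performance time |

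The recruitment-log sentence does not help, because it does not say whether the exclusions it covers come before or after randomization. The allowance for inadequate procedures suggests that some treated patients are expected to leave, but it does not define the population.

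**2. Inputs (Sample size section)**

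- Infraclavicular (ICB) mean 5 min 36 s = 336 s; RCB mean 4 min 29 s = 269 s; expected difference 67 s in favour of RCB.
- SD 2 min 18 s = 138 s in both groups.
- Margin 5% of ICB time: 0.05 × 336 = 16.8 s.
- One-sided alpha 0.05, power 0.90, 49 per group, target 55.

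**3. The plan's own figure**

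n = 2 × (1.645 + 1.282)² × 138² / (67 + 16.8)² gives 47 per group (48 with the noncentral t), within two of the stated 49. With a 10% allowance, 49/0.9 = 54.4, rounded up to 55. The stated figures reproduce, and this point does not alter them.

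**4. Power**

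Power = Φ[(67 + 16.8) / (138 × √(2/n)) − 1.645]

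| Analysed per group | Power |
|---|---|
| 55 | 0.938 |
| 52 | 0.927 |
| 49 | 0.913 |

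Loss of power is not the issue.

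**5. Bias (assumed exclusion counts and times)**

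Suppose k of 55 patients in an arm are excluded and their mean time is D longer than that of the rest. The arm's mean then falls by kD/55. If only RCB loses patients:

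| k | D = 60 s | D = 154 s | D = 300 s |
|---|---|---|---|
| 2 | 2.2 s | 5.6 s | 10.9 s |
| 4 | 4.4 s | 11.2 s | 21.8 s |
| 6 | 6.5 s | 16.8 s | 32.7 s |

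Here 154 s is 154/138 = 1.1 SD, and k = 6 is the protocol's own allowance (55 − 49).

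**6. Type I error when the true difference equals the margin**

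Error = 1 − Φ[1.645 − shift / (138 × √(1/n_RCB + 1/n_ICB))]

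- Four RCB and two ICB exclusions, D = 154 s: shift = (4 − 2) × 154/55 = 5.6 s; standard error = 138 × √(1/51 + 1/53) = 27.1 s; error about 0.075.
- Six RCB exclusions, no ICB, D = 154 s: shift 16.8 s; standard error = 138 × √(1/49 + 1/55) = 27.1 s; error 0.153.
- Range for RCB-only exclusions: 0.059 (k = 2, D = 60 s) to 0.331 (k = 6, D = 300 s).
- Equal numbers of the same kind in both arms: shift 0.

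**The case against.** **Per-protocol analysis is legitimate here.** In a non-inferiority trial, intention to treat alone can favour similarity, and excluding departures is a recognised approach. The allowance for inadequate procedures fits such an intent. This stands, and the remedy adopts it. It does not remove the contradiction, because the protocol never names a per-protocol set and also promises to analyse everyone randomized.

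**Detail belongs in an analysis plan that is not shown.** Full definitions of analysis sets commonly do. But this article itself states both rules, so the conflict is in the text rather than in what it omits.

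**The bias mechanism is conjecture.** The needle, drugs and volumes are the same in both arms. Difficult blocks can be handled within protocol by dextrose hydrolocalization, neurostimulation, tip adjustment and further passes, none of which triggers exclusion. The text does not say that departures would concentrate in slow RCB blocks. This stands, and for that reason the figures are only illustrative. The six-exclusion case also stacks assumptions: all losses in one arm, each averaging 1.1 SD longer, and a true difference exactly at the margin. Under the protocol's own expectation that RCB is 67 s faster, non-inferiority is true, and a 16.8 s shift would create no false claim.

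**A stronger reading that a reader might infer** is that the exclusion rule, having no stated exemption, also deletes failed blocks rescued with local anaesthetic and so inflates the success rate. The documents do not support this. The needle, drug and dose list mirrors the initial study block. The outcome definition reads "Success is defined as the completion of surgery without the need for additional LA infiltration, intravenous narcotics, or general anaesthesia", so rescued patients must stay in to be counted as non-successes. Supplemental blocks are offered under the protocol when the sensory score is below 9/10 at 30 minutes. The concomitant-care section also treats sedation beyond its limits as a block failure rather than a reason for exclusion. At most, a clarifying word would help.

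**Conclusion.** The point holds. Two stated rules conflict on whether randomized patients with needle, drug or dose departures, or too sedated to be tested, are analysed. The intention-to-treat sentence does not resolve the conflict for the primary outcome.

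The size cannot be determined from the document, which gives no deviation rates. For D = 154 s and a true difference at the margin, the illustration runs from no bias with balanced exclusions, through a 5.6 s shift and about 7.5% type I error for a net excess of two RCB exclusions, to 16.8 s and about 15% for six RCB-only exclusions. Power stays above 0.91 throughout the protocol's allowance. The text does not show that the trial will be biased towards RCB; it shows that the population for its main claim is undefined and open to exclusions that depend on what happened after allocation.

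**What to change.** - **Intervention – concomitant care:** apply the needle, drug and dose rule to the initial study block only, and let it define a per-protocol set instead of exclusion from the analysis. For a patient too sedated to cooperate, treat only the sensory and motor scores as missing and keep performance time.
- **Statistical methods:** state that all randomized patients are analysed as allocated, that performance time is tested in both the intention-to-treat and per-protocol sets, and that non-inferiority is claimed only if both agree.

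**Cost:** a few sentences and one extra analysis set. Applying the present exclusion rule already requires needle, drug and dose to be known, so no new data are needed, and patient care does not change. The claim becomes slightly stricter: the power to succeed in both sets cannot exceed that of the smaller one, 0.913 if the per-protocol set falls to 49 per group, which is still above the planned 0.90. The two sets would share most of their patients, so the further loss should be small.

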#### Sample size

We decided to conduct a non-inferiority trial with the aim of demonstrating that performance time for the RCB approach is no longer than for the coracoid ICB approach. On the basis of a recent study [15], we established that the performance time for the coracoid ICB approach is 5 min 36 s, with 45 s of visualization time. On the basis of the feasibility trial recently conducted, needling time for the RCB approach is 3 min 42 s [11]. If we use the same imaging time of 45 s, we expect a performance time of 4 min 29 sec for the experimental approach. The standard deviation used for both groups was 2 min 18 s, as reported in the literature [15]. We deemed that a time superiority of 5% would be significant. In other words, RCB performance time will be deemed non-inferior to ICB if the upper margin of the 95% confidence interval created around RCB performance time is under the ICB performance time plus 5%. When using these hypotheses to conduct a non-inferiority analysis, a calculated sample size of 49 patients per group will be required to provide statistical power of 0.90 and one-sided type I error of 0.05. To compensate for potential dropouts or inadequate procedures, we will aim for a sample size of 55 patients per group.

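### The plan both excludes protocol-deviating patients from the analysis and includes every randomised patient in it, so the population for the primary non-inferiority test is contradictory

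*Protocol article*

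**What the plan says.** Four statements in the protocol article bear on who enters the primary analysis.

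- *Intervention – concomitant care*, on deviations: if another needle, another local anaesthetic or "other volume/dose of local anaesthetics are used, the patient will be excluded from the analysis".
- The same section, on patients who received more than 2 mg of midazolam or an equivalent: "the patient will be included only if he is still able to adequately collaborate during the evaluation of motor and sensory blockade".
- *Allocation concealment mechanism*: "When the numbered envelope is opened, the patient is automatically included in the analysis". The same paragraph provides for a recruitment log in which "exclusion will be justified for each patient excluded", without saying whether these exclusions fall before or after randomisation.
- *Statistical methods*: "performance time will be analyzed with a non-inferiority test of the averages", with no analysis set named. Later in that section: "If data are missing or if any patients drop out of the study, data will be analyzed using the intention-to-treat principle".

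*Sample size* raises the target from 49 to 55 per group to cover drop-outs and inadequate procedures. That suggests some randomised patients were expected to be lost from the analysis.

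**The concern.** The choice of needle, drug and volume is carried out after the envelope is opened. A patient with such a deviation is therefore automatically included under one section and excluded under another, and nothing says which rule governs. The intention-to-treat sentence does not settle it, because a patient with a deviation and a recorded time is neither missing nor a drop-out.

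This reaches the primary outcome. Performance time is imaging time plus needling time, and needling runs from the skin wheal to removal of the needle. A change of needle or drug volume happens inside that interval, and the operator knows the allocation. The patients removed could plausibly have unusual times, possibly more in one arm than in the other. Following the exclusion rule as written then breaks the randomised comparison.

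The sedation condition concerns cooperation with block testing at 10 to 30 minutes, by which time performance time is complete. It gives no reason to drop a patient from the time analysis.

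**Working it through.** **Inputs, all from *Sample size*.** Control: "the performance time for the coracoid ICB approach is 5 min 36 s, with 45 s of visualization time", so 336 s. Experimental: "needling time for the RCB approach is 3 min 42 s", plus 45 s of imaging; the article states the total as 4 min 29 s = 269 s (the components add to 267 s). SD 138 s in both groups. Margin 5% × 336 = 16.8 s. One-sided alpha 0.05, power 0.90, 49 per group, raised to 55.

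**The plan's own figure.** Planned difference 269 − 336 = −67 s, so the distance to the margin is 16.8 + 67 = 83.8 s. n = 2 × 138² × (1.645 + 1.282)² / 83.8² = 46.5, so 47 per group, or 48 with the t distribution. This is within two patients of 49, so the sample size is not in dispute here. The inflation leaves room to lose 6 of 55 (10.9%) per arm.

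**Shift from selective exclusion.** If times are normal and the k slowest of 55 are removed from one arm, that arm's mean falls by 138 × φ(z)/p, with p = 1 − k/55 and z = Φ⁻¹(p).

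- k = 3: p = 0.945, z = 1.602, φ = 0.1105, fall = 16.1 s.
- k = 6: p = 0.891, z = 1.231, φ = 0.1869, fall = 29.0 s.

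Three such exclusions shift the mean by about the whole margin.

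**Error rate when the true difference equals the margin.** SE = 138 × √(2/49) = 27.9 s.

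- Slowest removed from the retroclavicular arm only: Φ(−1.645 + 16.1/27.9) = 0.14 for 3, and Φ(−1.645 + 29.0/27.9) = 0.27 for 6.
- Slowest removed from the infraclavicular arm only: Φ(−1.645 − 16.1/27.9) = 0.013 for 3, and Φ(−1.645 − 29.0/27.9) = 0.004 for 6. Planned power falls from Φ(83.8/27.9 − 1.645) = 0.91 to Φ((83.8 − 29.0)/27.9 − 1.645), about 0.63, for 6.

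These are approximations: they leave the SD untruncated and use 49 in both arms.

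**Simulation check.** 40,000 trials, 55 per arm before exclusions, true difference at the margin, t test at one-sided 0.05. Where two values are shown, they are for normal and lognormal times.

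| Exclusion pattern | 3 excluded | 6 excluded |
|---|---|---|
| Slowest, retroclavicular arm only | 0.16–0.21 | 0.31–0.42 |
| At random from the slowest quarter, retroclavicular arm only | 0.10 | 0.20–0.21 |
| Slowest, each arm | 0.07 | 0.08–0.09 |

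With no exclusions the rate is 0.05. Under the first pattern with 3 excluded, the mean falls by 15.5 s (normal) to 19.9 s (lognormal). Exclusions unrelated to time leave the test unbiased, and 49 per arm still gives power 0.91, against 0.94 with all 55.

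**The case against.** A reader might infer that the exclusion rule favours non-inferiority. The article does not support that. It would do so only if slow retroclavicular blocks were excluded more often than slow infraclavicular ones. The article's own expectation is that infraclavicular blocks take longer (5 min 36 s against 4 min 29 s) and that needle visualization is their weak point. If slow infraclavicular blocks were the ones dropped, the bias would run against the new approach. This objection stands: the direction is unknown.

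The size is also open. No exclusion rate is given. The allowance of 6 per arm covers drop-outs and inadequate procedures together, so it is not a count of deviation exclusions. No statement links deviations to difficulty; that link is plausible but assumed. The one-arm, slowest-patient pattern is extreme, and the formula results of 0.14 and 0.27 are not an upper bound even for that pattern, since simulation gives more.

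A reader might also see a three-way contradiction with intention-to-treat. That principle is stated only for missing data and drop-outs, so the firm conflict is between the concomitant-care and allocation-concealment sections. The sedation sentence does not say which analysis it restricts, and exceeding the allowed sedation is classed as block failure, which is an outcome and not an exclusion.

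Finally, detailed set definitions are commonly left to an analysis plan that is not shown. That excuses missing detail, but not two incompatible rules in the published text. The exclusion rule cannot simply be read as defining a per-protocol set, because none is mentioned and the rule refers to the analysis without qualification.

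**Conclusion.** The contradiction is established from the text: the same randomised patient is included by one section and excluded by another, and no section names the set for the primary test.

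The effect on the result is a possibility and not a prediction. Any bias requires exclusions that are related to performance time and that do not affect the arms equally in size and pattern; its direction could be either way. If those conditions hold, few exclusions are needed, because the margin is about an eighth of the SD (16.8/138 = 0.12). With 3 of 55 removed, the error at a nominal 0.05 could lie anywhere from about 0.01 (slowest infraclavicular patients only) to 0.21 (slowest retroclavicular patients only). It is about 0.07 when both arms lose their slowest 3, and 0.05 when exclusions are unrelated to time. These figures assume normal or lognormal times, an SD of 138 s, and exclusion counts chosen for illustration.

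**What to change.** 1. In *Intervention – concomitant care*, replace the exclusion from the analysis. State there and in *Statistical methods* that the primary performance-time analysis includes all randomised patients with a recorded time, analysed as allocated. This agrees with *Allocation concealment mechanism*. Report by arm any randomised patient without a recorded time.
2. Use the needle, drug, volume and dose deviations only to define a per-protocol set, classified from the data forms before results by arm are seen. This needs stating because the statistician is not blinded.
3. Report the per-protocol result alongside as a supporting non-inferiority analysis and discuss whether it agrees with the primary one. An intention-to-treat analysis is not automatically conservative for non-inferiority, so the second set is informative. Requiring success in both sets is a reasonable stricter option, but not a necessity.
4. Apply the sedation and cooperation condition only to the sensory and motor scores, not to performance time.

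The cost is a change of wording and one additional analysis. The research assistant times the blocks by chronometer, so the times of affected patients should already exist. A quarter of the calculated sample had been recruited at submission and no interim analysis is planned, so the set can be fixed before results are known.

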### Objectives

Our general objective is to make a formal comparison between RCB [10, 11] and coracoid ICB for brachial plexus anaesthesia. This study will delineate the differences between the two techniques. Our aim is to compare both techniques in terms of scanning time, needling time, total anaesthesia time, needle visibility, block needle passes, block success and early and late complications. We made the hypothesis that, while providing similar efficacy and better needle visualization than coracoid ICB, the time taken to perform RCB will not exceed the time taken to perform its comparator [3].

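### The rule that drops patients given another needle, agent or local anaesthetic dose exempts no outcome, so it can remove a complication during the block from its own reported incidence

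*Protocol article*

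**What the plan says.** Five parts of the protocol article bear on who is counted.

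- **Intervention – concomitant care.** Strict adherence is required. If another needle or agent, or "other volume/dose of local anaesthetics are used, the patient will be excluded from the analysis". The rule names no outcome to which it does not apply.
- **Allocation concealment mechanism.** "When the numbered envelope is opened, the patient is automatically included in the analysis". The section then provides for a recruitment log in which "exclusion will be justified for each patient excluded".
- **Statistical methods.** "If data are missing or if any patients drop out of the study, data will be analyzed using the intention-to-treat principle". Deviations in needle, agent or dose are not mentioned.
- **Sample size.** "To compensate for potential dropouts or inadequate procedures, we will aim for a sample size of 55 patients per group". The term for inadequate procedures is not defined.
- **Objectives and Secondary outcome measures.** The comparison covers "needle visibility, block needle passes, block success and early and late complications", and "the incidence of needle-induced paresthesia, vascular puncture, Horner syndrome, dyspnea, and symptoms of LA toxicity will be noted". No denominator is given.

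The study injection is 20 ml of mepivacaine plus 20 ml of ropivacaine. According to Needling and injection, these "will be injected in a fractionated way, while slightly adjusting the needle tip".

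**The concern.** The exclusion is applied after randomisation and is defined by what was actually given. For performance time that is a familiar question of intention-to-treat against per-protocol analysis. For complications there is a further difficulty, because the event may itself cause the deviation. The injectate is given in fractions. If the operator stops because the patient reports symptoms of local anaesthetic toxicity, the patient has received another volume. Taken literally, the rule then removes that patient from the comparison in which the event should count.

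At stake is the descriptive safety comparison of a newer approach with the established one. The Harms section says that the trial is not expected to have the power to show differences in complications. The per-arm counts are therefore the main safety information, and one event more or less is visible in them.

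**Working it through.** **Step 1: which rule governs a randomised patient with a deviation?**

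- Concomitant care: out of the analysis.
- Allocation concealment, statement on envelopes: in the analysis.
- Allocation concealment, statement on the log: exclusions may occur if justified, with no rule for which exclusions or which outcomes.
- Statistical methods: intention to treat for missing data and dropouts, silent on deviations.
- Sample size: the allowance for inadequate procedures suggests that some randomised patients are expected to be left out.

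The texts can be read together as inclusion by default with logged exclusions. On that reading the concomitant-care exclusion applies, and it applies to complications too, because nothing exempts them.

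**Step 2: which events can trigger the exclusion?** Only those that lead the operator to change the needle, the agent or the amount injected. A patient whose needle is realigned after vascular puncture or paresthesia and who then gets the full dose stays in. Complications that first appear by the 48-hour call cannot have altered the injection.

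**Step 3: the plan's own figures.** Inputs from Sample size: 5 min 36 s (5.60 min) for coracoid ICB, 4 min 29 s (4.483 min) expected for RCB, SD 2 min 18 s (2.30 min), margin 5% of 5.60 = 0.28 min, one-sided 0.05, power 0.90.

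n = 2 × (1.645 + 1.282)² × 2.30² / (0.28 + 1.117)² = 46.4, so 47 per group (48 with the noncentral t), close to the stated 49. The sample size is not in dispute. The figure of use here is the allowance: 55 − 49 = 6 per group, and 6/55 = 10.9%, for dropouts and inadequate procedures together.

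**Step 4: size of the effect.** The document gives no complication or deviation rates. The event counts and the 1 to 6 exclusions per arm below are therefore assumptions. Intervals are exact (Clopper-Pearson), two-sided 95%.

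| Assumed case, one arm of 55 | All patients kept | After exclusion |
|---|---|---|
| 6 exclusions, none with the event | 1/55 = 1.8% | 1/49 = 2.0% |
| 6 exclusions, none with the event | 2/55 = 3.6% | 2/49 = 4.1% |
| 1 exclusion, triggered by the event | 1/55 = 1.8% (0.05% to 9.7%) | 0/54 (upper limit 6.6%) |
| 6 exclusions, 1 triggered by the event | 1/55 = 1.8% | 0/49 (upper limit 7.3%) |
| 1 exclusion, triggered by the event | 2/55 = 3.6% | 1/54 = 1.9% |
| 6 exclusions, 1 triggered by the event | 2/55 = 3.6% | 1/49 = 2.0% |

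**Step 5: direction.** Let e be the events in 55, x the exclusions, and t the excluded patients who had the event. Then (e − t)/(55 − x) < e/55 exactly when t/x > e/55. With t = 0 and e above zero the incidence always rises. With t = 1 and x = 6 it falls while e < 55/6 = 9.2, that is for up to 9 events, and rises from 10. So the direction is not fixed, although for rare events a single triggered exclusion lowers the incidence.

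**Step 6: tests.** With all patients kept, two-sided Fisher tests against 0/55 give p = 1.00 for 1/55 and p = 0.50 for 2/55. No significance result at these counts turns on the exclusion.

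**The case against.** The strongest case on the other side has five parts.

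- **The two rules can be reconciled.** The section that includes every opened envelope also provides for justified exclusions. This stands: a reader might infer a flat contradiction, but the text allows default inclusion with logged exclusions. That reading leaves the complications problem in place, because the exclusion still exempts no outcome.
- **The mechanism is inferred.** The protocol describes no early stop, and its wording on another dose may be aimed at the choice of a different regimen. This also stands. The point is only that the rule, as worded, can catch an interrupted injection.
- **Harms are captured anyway.** All patients are called at 48 hours, any complication goes on the data collection form, and exclusions are logged. A reader might infer that events would be lost or hidden; the documents do not support that. These provisions govern collection, however, and do not say who forms the numerator and denominator of the incidence.
- **The set could still be fixed in time.** Only a quarter of the sample had been recruited at submission, and a fuller protocol or SAP may exist. A reader might infer that the set must be chosen once the events are known; that does not follow. What remains is that the exclusion as published is explicit and covers every outcome.
- **The conflict reaches further than complications.** It also bears on which patients count for performance time and block success. That is true, but it is a separate question, and the fix given here does not settle it.

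**Conclusion.** The point holds in a limited form. As written, the exclusion can remove a patient from the complications comparison because of an event during needling or injection, and the text does not settle whether it applies once the envelope has been opened. The consequence is confined to the reported per-arm incidence of such events.

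A reader might infer that the rule makes the retroclavicular approach look safer, or that it distorts the complications comparison as a whole. The documents support neither. The rule applies to both arms, excluding event-free patients pushes the incidence slightly the other way, and late complications cannot trigger it.

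Under the assumed counts the change is one event in an arm, for example 1.8% to none, or 3.6% to about 2%. The effect is probably small and no significance result depends on it. The conclusion rests on a literal reading of the dose rule and on the inference that an operator might stop or alter an injection because of symptoms. It is a correction worth making because it is cheap, not because a result is at risk.

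**What to change.** State under Intervention – concomitant care and again under Statistical methods that the exclusion does not apply to early and late complications. Report these by assigned arm in all randomised patients in whom the block needle was inserted, whatever needle, agent, volume or dose was used. Add a table row listing uncompleted or altered injections per arm, with reasons taken from the exclusion log.

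The cost is one or two sentences and one table row. No new patients, visits or data are needed, since the events are already on the data collection form and in the 48-hour call, and exclusions are already to be justified. The downside is that a few reported events will come from patients who did not receive the full study injection; the added row lets the reader see which arm they belong to and why.
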